#### 18.1.2 Secondary study parameters/endpoints

##### Work Package 1

All analyses will be performed uncorrected as well as corrected for age, nutritional status and risk categories and type and severity of illness. Time-to-event analysis will be analyzed similarly as the primary endpoint. Proportion of patients requiring support of vital organ functions and distribution of duration of support will be analyzed by non-parametric or parametric testing depending on the normality of the distribution in the subgroup of patients for which support was needed. Proportions will be compared using chi-square testing. Results of repeated measurements will be analyzed using an appropriate model for longitudinal data.

a. Time to final (alive) weaning from mechanical respiratory support: patients still on

mechanical respiratory support at closing of the data file (90 days after last patient

inclusion) will be censored at that time point. ICU non-survivors will be censored

beyond the longest duration of mechanical respiratory support of the survivors.

b. Kidney failure: Proportion of patients in need for renal replacement therapy (RRT)

during ICU stay; distribution of duration of RRT (for those patients requiring RRT);

proportion of patients with a post-randomization diagnosis of new kidney injury/failure

(defined by modified Risk, Injury, Failure, Loss, and End-stage Kidney (RIFLE)

classification criteria as a plasma creatinine doubling or more during ICU stay) in both treatment groups. In addition, the duration of a score RIFLE $\geq$ 2 will be used as a marker of time to recovery of kidney damage.

c. Need for pharmacological or mechanical haemodynamic support during ICU stay, and duration of such need.

In addition, time to final (alive) weaning from all pharmacological or mechanical haemodynamic support in ICU will be analyzed, with ICU non-survivors censored beyond the longest duration of pharmacological or mechanical haemodynamic support of the survivors and censoring time of patients still on such support at closing of the data file (90 days after last patient inclusion) over both treatment groups.

d. Number of readmissions to the PICU.

e. Liver dysfunction: Proportion of patients during the time window of the intervention and during the whole ICU stay presenting with cholestatic or cytolytic liver dysfunction will be compared.

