## **18.2 Randomisation, blinding and treatment allocation**

### ***Randomization***

The study will use a prospective, randomized, controlled, parallel-group design. On admission patients will be randomly assigned to receive EN combined with early PN or only EN. At ICU admission, consecutive patients will be randomly assigned to one of these two treatment groups using a centralized computer randomisation. Randomisation will be done in a 1:1 allocation ratio in permuted blocks of 10 (The block size remains unknown to bed-side physicians and nurses, responsible for patient recruitment and therapy assignment) and stratified according to primary diagnostic category on admission:

I Medical-ICU admissions (infectious or non-infectious): (a) respiratory (b) cardiac (c) renal (d) haematological/oncological (e) gastro-intestinal/hepatic (f) neurological (g) other.

II Surgical-ICU admissions (elective or urgent) according to referral discipline (a) cardiac surgery (b) solid organ transplants (c) pulmonary/oesophageal surgery (d) abdominal surgery (e) neurosurgery (f) trauma/orthopaedic surgery (g) burns (more than 20% BSA is burned and/or patient requires ventilation)

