## **20.3 Multivariate analysis**

All outcomes will be analyzed in an uncorrected manner as well as (jointly) corrected for risk factors (type and severity of illness, age, on admission nutritional status and risk scores). Another *a priori* defined subgroup analysis will be performed for patients admitted to ICU after cardiac surgery as compared with all other patients. Also an *a priori* subgroup analysis is planned for patients with and without sepsis upon admission.

All analyses will be performed uncorrected as well as corrected for age, nutritional status and risk categories and type and severity of illness. Time-to-event analysis will be analyzed similarly as the primary endpoint. Proportion of patients requiring support of vital organ functions and distribution of duration of support will be analyzed by non-parametric or parametric testing depending on the normality of the distribution in the subgroup of patients for which support was needed. Proportions will be compared using chi-square testing. Results of repeated measurements will be analyzed using an appropriate model for longitudinal data.

a. Time to final (alive) weaning from mechanical respiratory support: patients still on mechanical respiratory support at closing of the data file (90 days after last patient inclusion) will be censored at that time point. ICU non-survivors will be censored beyond the longest duration of mechanical respiratory support of the survivors.

b. Kidney failure: Proportion of patients in need for renal replacement therapy (RRT) during ICU stay; distribution of duration of RRT (for those patients requiring RRT); proportion of patients with a post-randomization diagnosis of new kidney injury/failure (defined by modified Risk, Injury, Failure, Loss, and End-stage Kidney (RIFLE) classification criteria as a plasma creatinine doubling or more during ICU stay) in both treatment groups. In addition, the duration of a score RIFLE $\geq$ 2 will be used as a marker of time to recovery of kidney damage.

c. Need for pharmacological or mechanical hemodynamic support during ICU stay, and duration of such need.

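### The proportions for liver dysfunction, haemodynamic support and RRT count children already affected at randomisation, which dilutes these secondary comparisons

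*Supplement*

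**What the plan says.** The definitions are in the final protocol, section 18.1.2 (Work Package 1, items b, c and e), and are repeated in section 20.3.

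- **RRT (item b):** "Proportion of patients in need for renal replacement therapy (RRT) during ICU stay", with duration among those who receive it.
- **Haemodynamic support (item c):** "Need for pharmacological or mechanical haemodynamic support during ICU stay, and duration of such need".
- **Liver dysfunction (item e):** "Proportion of patients during the time window of the intervention and during the whole ICU stay presenting with cholestatic or cytolytic liver dysfunction".

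Proportions are compared by chi-square, uncorrected and corrected for age, nutritional status and risk, and type and severity of illness. Section 20.1 sets significance at p below 0.05 for all endpoints, without multiplicity correction.

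Section 18.2 places randomisation at ICU admission. None of the three proportions is limited to onset after that moment.

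Other outcomes are limited in this way. Item b also has the "proportion of patients with a post-randomization diagnosis of new kidney injury/failure". Section 14 requires that a nosocomial infection was neither present nor incubating at PICU admission. Section 18.1.1 counts only antibiotic therapy started after randomisation.

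The one SAP in the supplement covers a later analysis of undernourished children. It does not list or redefine these three outcomes.

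**The concern.** A child who comes from cardiac surgery on an inotrope that is stopped on day 1 is an event under item c. A child admitted with cholestasis is an event under item e, in the intervention window and over the whole stay. Feeding allocation can neither cause nor prevent either event. Such children appear in both arms, raise both proportions and bring them closer together.

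The case mix makes this plausible. Section 15.1 reports that 61% of the 2010 Leuven PICU admissions followed cardiac surgery, and the strata in section 18.2 include solid organ transplant, renal and gastro-intestinal/hepatic admissions. The protocol's rationale names hepatic steatosis among the complications associated with PN, so new liver dysfunction is an outcome on which the intervention could act. A null comparison of any-time proportions would be weak evidence against such an effect, yet it could be read as reassurance.

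**Working it through.** **The plan's own figure.** Section 15.4 gives 720 per arm to detect 20% versus 15% new infections, with at least 80% power one-tailed and 70% two-tailed. With the normal approximation

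power = Φ{ [d − z·√(2p̄(1−p̄)/n)] / √([p₁(1−p₁) + p₂(1−p₂)]/n) },

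d = 0.05, p̄ = 0.175, n = 720 and z = 1.96, this is Φ{(0.0500 − 0.0393)/0.0200} = 0.705. The one-tailed value is 0.803. Both stated figures reproduce.

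**Inputs for the dilution check.** The documents give no event rate for any of the three outcomes and no share affected on arrival. The following are therefore assumptions:

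- q, the share already affected at randomisation, equal in both arms in expectation;
- new events of c = 20% versus t = 15% among the remaining children, borrowed from the infection endpoint.

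The 720 per arm and two-sided 0.05 are the plan's.

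**Formulas.** As written, each observed proportion is P = q + (1−q) × incident risk, so the absolute difference is (1−q)(c−t), tested on 720 per arm. For new onset only, c is compared with t on 720(1−q) per arm.

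| q | Observed, as written | Difference | Risk ratio | Power as written | n per arm, new onset | Power, new onset |
|---|---|---|---|---|---|---|
| 0% | 20.0% vs 15.0% | 5.0 points | 0.75 | 70% | 720 | 70% |
| 2% | 21.6% vs 16.7% | 4.9 | 0.77 | 66% | 706 | 70% |
| 5% | 24.0% vs 19.25% | 4.75 | 0.80 | 59% | 684 | 68% |
| 10% | 28.0% vs 23.5% | 4.5 | 0.84 | 50% | 648 | 66% |
| 20% | 36.0% vs 32.0% | 4.0 | 0.89 | 36% | 576 | 61% |
| 30% | 44.0% vs 40.5% | 3.5 | 0.92 | 27% | 504 | 55% |
| 50% | 60.0% vs 57.5% | 2.5 | 0.96 | 16% | 360 | 42% |

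**Why the smaller sample does better.** Apart from the variance term, both analyses carry the same signal, √(1−q)·(c−t)·√n. For new onset the variance term per arm is c(1−c). As written it is (1−c)(q + (1−q)c), which is larger by q(1−c)². At q = 20% the two arms sum to 0.160 + 0.1275 = 0.2875 for new onset and 0.288 + 0.272 = 0.560 as written. The excess is the random scatter in how many affected children each arm receives.

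**Other rates.** With new events of 10% versus 5%, power as written against new onset is 79% vs 94% at q = 5%, 41% vs 90% at 20% and 21% vs 80% at 40%.

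**The case against.** The strongest reply is that the any-time proportion is a valid intention-to-treat contrast. Affected children are balanced in expectation, so neither arm gains. That is right. The point concerns sensitivity, and only in secondary endpoints.

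Items b and c also keep measures that remain sensitive. Item c adds duration, and "time to final (alive) weaning from all pharmacological or mechanical haemodynamic support in ICU will be analyzed". Children who arrive on support contribute validly to both. Item b adds RRT duration, duration of RIFLE stage 2 or worse, and new kidney injury. This stands, and it limits the harm for these two items. It does not repair the proportions, which are tested in their own right. Item e names no companion measure. Liver tests are on the daily morning sample and section 18.1.2 provides for longitudinal models, but item e does not call for one. Its second window, the intervention period, still includes children affected on arrival.

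Correction for type and severity of illness, and analyses by diagnostic category, help in part. Presence of the condition at randomisation is not a named covariate, and one category can hold both affected and unaffected children.

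A new-onset proportion also answers a narrower question, since it leaves out children whose existing support is prolonged. That is why the duration and weaning analyses should stay, in all children.

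A reader might infer that the rule masks any effect, or that the proportions are mostly baseline prevalence. The documents support neither. They give no baseline share, and at q = 2% the cost is about 4 percentage points of power. The 61% figure covers all admissions at one of three centres in one year. It does not show how many randomised children were on support, and it says nothing about RRT or liver dysfunction on arrival.

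**Conclusion.** The point holds as a loss of sensitivity in three secondary proportions. Children affected at randomisation are automatic events, so the difference shrinks by (1−q) and the risk ratio moves towards 1. Under the assumed 20% versus 15%, the cost is slight at q = 2%, 16 points of power at 10%, 25 points at 20% and 28 points at 30%. The table is an illustration: both q and the incident rates are assumed.

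The point is strongest for liver dysfunction, which has no companion measure. Haemodynamic support comes next: the cardiac-surgery case mix makes a sizeable q plausible, but duration and alive-weaning analyses exist. It may be small for RRT. The primary endpoints are not affected and no arm is favoured.

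**What to change.** Change sections 18.1.2 and 20.3 of the protocol. The undernutrition SAP is not the place, because it does not cover these outcomes.

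- For item e, make the tested proportion newly arising liver dysfunction after randomisation, among children without it at randomisation. Apply the outcome's own laboratory criteria to the admission sample.
- For item c and the RRT part of item b, make it support newly started after randomisation, among children not on that support at randomisation.
- Report the any-time proportions descriptively.
- Leave the duration and alive-weaning analyses unchanged, in all children.

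The subset is defined by status at randomisation, so the randomised comparison is preserved. Section 18.3 already provides for admission and daily blood samples with liver tests, a baseline record of liver and kidney failure, and the need for and days of support. Support status at the moment of randomisation is not listed as a separate item and would have to be derived from these records. The cost is a smaller denominator for each restricted comparison and one extra line per table.

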f. Inflammation: Effect of the intervention on inflammation will be analyzed by comparing the distribution of the highest value reached during ICU stay and changes from baseline to the highest value and by comparing time profiles of daily C-Reactive Protein values.

g. Child health questionnaire scores in both treatment groups will be compared at 3 and 12 months post-discharge.

h. Enteral nutrition (EN) tolerance: proportion of patients with diarrhoea, high gastric residual volumes, vomiting and/or abdominal swelling and relation with buccal epithelial cell expression of chemokines (CXCL-8, CXCL-9 and CXCL-10)

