#### Blood samples

The maximum blood volume will be maximum 5 ml/kg for the entire study period. For a detailed description of the blood samples and tests see figure below. Blood samples are taken upon ICU admission and daily until discharge from ICU, or death. The blood samples will be taken from lines placed for clinical purposes or in combination with pricks requested for clinical purposes. A subset of the samples are immediately stored on ice for future endocrine measurements. Processed serum and plasma as well as the spun-down blood cells will be stored and frozen for mechanistic analyses.

All whole blood glucose levels are measured on arterial blood using a blood gas analyser on each ICU and are registered for later calculation of glucose metrics. Analyses on blood and urine for the primary clinical analyses include routine chemistry, haematology, and markers of inflammation. Further epigenetic, metabolic, endocrine and inflammatory measurements on stored samples in the context of mechanistic analyses will be stored until final analysis. Urine samples will be stored and frozen until final analysis.

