### ***General rules of the statistical analysis***

All analyses will be done on intention to treat basis. The analyses will be performed on the whole set of patients and by subgroups of patients based on the primary diagnostic categories used as prognostic factors for stratification and on septic/non-septic groups of patients.

A consort diagram will be reported. The data file will be finalised 90 days after inclusion of the last patient. To assess compliance with the study protocol, the amounts of PN and EN actually given in the two study groups during the intervention window of 7 days will be reported as absolute numbers and percentages of target calories. Discrete variables will be summarised by frequencies and percentages and analysed by (exact) Chi- square test or logistic regression analysis. Continuous variables will be summarised by use of either mean or standard deviations (SD) or median and interquartile range as appropriate and compared using Student's t-test or Mann-Whitney-U test, as appropriate. Time to event analysis will be performed by Cox proportional hazard analysis. All outcomes will be analysed in an uncorrected manner as well as (jointly) corrected for risk factors (type and severity of illness, age, on admission nutritional status and risk scores). *A priori* defined subgroup analyses will be performed for patients admitted to ICU after cardiac surgery as compared with all other patients; for patients with and without sepsis upon admission; for patients with contra-indications for EN on admission or not. For all endpoints, differences will be considered statistically significant whenever the p-value is lower than 0.05 without correction for multiple testing.

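### The CRP peak and change comparisons do not adjust for admission CRP, and the peak may be the admission value itself: a small, conditional loss of precision on a secondary endpoint

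*Supplement*

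**What the plan says.** In the final protocol, item f of section 18.1.2 (Work Package 1), repeated in 20.3, sets three comparisons of inflammation between the arms. Two are given as "comparing the distribution of the highest value reached during ICU stay and changes from baseline to the highest value". The third is made "by comparing time profiles of daily C-Reactive Protein values".

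The adjustment rule in 18.1.2 is: "All analyses will be performed uncorrected as well as corrected for age, nutritional status and risk categories and type and severity of illness". The general rules in 20.1 and the text of 20.3 list essentially the same risk factors. None of these lists names the admission value of the outcome. For continuous outcomes in general, 20.1 says they are "compared using Student's t-test or Mann-Whitney-U test, as appropriate". For serial data, 18.1.2 says: "Results of repeated measurements will be analyzed using an appropriate model for longitudinal data". How that model treats baseline is not stated.

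On sampling, section 18.3 says: "Blood samples are taken upon ICU admission and daily until discharge from ICU, or death". CRP is named among the analyses of the morning sample (18.3, text to the samples figure). An admission CRP is implied by the planned change from baseline rather than stated outright.

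The SAP in the supplement covers a later secondary analysis of undernourished children. CRP is not among its outcomes, so it does not add to item f.

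**The concern.** Two things are at issue.

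**Precision.** A raw peak ignores where the child started, and a change score subtracts the whole of the starting value. A model with admission CRP as a covariate estimates how much to subtract and, in a randomised comparison, is in large samples at least as precise as either. The value needed should already be in the data, because the change score depends on it.

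**Definition.** The peak is taken over the ICU stay, the admission sample falls within that stay, and nothing excludes it. A child whose CRP only falls then has a peak that was fixed at about the time of randomisation. The matching change is zero however fast the fall. The change score has a floor at zero and cannot show one arm settling more quickly than the other.

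At stake is some sensitivity to an effect on inflammation in a named secondary endpoint. The primary endpoints and the validity of the randomised comparison are not affected.

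**Working it through.** **1. The plan's own power figure.** No power is stated for CRP. The only figure that can be reproduced is for infections, 20% against 15% with 720 per arm (15.4). With pooled variance and no continuity correction, this gives 80.3% one-tailed and 70.5% two-tailed, against the stated 80% and 70%. These figures do not carry over to CRP. Below, 70% and 80% serve only as assumed starting powers.

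**2. The floor at zero.** Let A be the admission CRP and M the highest later value. Peak = max(A, M), so change = max(A, M) − A = max(0, M − A). This is never negative, and it is 0 whenever M ≤ A. No assumed figure is needed.

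**3. Relative precision.** Inputs from the documents: 720 per arm, and alpha from 20.1 ("differences will be considered statistically significant whenever the p-value is lower than 0.05 without correction for multiple testing"), taken as two-sided. Assumptions: complete data, roughly normal values, equal SDs at baseline and peak, and correlation ρ between them. Variances relative to the raw peak are:

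- raw peak: 1
- change score: 2(1 − ρ)
- adjusted for admission CRP: 1 − ρ²

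Power = Φ((z + 1.96)/√variance − 1.96), where z is 0.524 for a raw-peak power of 70% and 0.842 for 80%. At ρ = 0.5 the variances are 1, 1 and 0.75, so:

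- from 70%: 2.484/0.866 − 1.96 = 0.909, power 81.8%
- from 80%: 2.802/0.866 − 1.96 = 1.275, power 89.9%

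The same formula over a range of assumed ρ gives (in %, with gains in points taken before rounding):

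| ρ | Raw 70: change | Raw 70: adjusted | Gain over better | Raw 80: change | Raw 80: adjusted | Gain over better |
|---|---|---|---|---|---|---|
| 0.2 | 50.2 | 71.8 | 1.8 | 60.1 | 81.6 | 1.6 |
| 0.3 | 55.6 | 74.0 | 4.0 | 65.8 | 83.6 | 3.6 |
| 0.4 | 62.1 | 77.4 | 7.4 | 72.5 | 86.4 | 6.4 |
| 0.5 | 70.0 | 81.8 | 11.8 | 80.0 | 89.9 | 9.9 |
| 0.6 | 79.3 | 87.4 | 8.1 | 87.9 | 93.8 | 5.9 |
| 0.7 | 89.4 | 93.6 | 4.2 | 95.1 | 97.5 | 2.4 |
| 0.8 | 97.5 | 98.5 | 1.0 | 99.3 | 99.7 | 0.3 |

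The better planned comparison is the raw peak below ρ = 0.5 and the change score above it. The gain over the better one is largest at ρ = 0.5.

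**4. Beyond the planned correction.** Suppose the listed covariates explain R² of the variance and admission CRP adds ΔR². Power = Φ((z + 1.96)/√(1 − R² − ΔR²) − 1.96). Both R² and ΔR² are assumed.

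| Raw power | R² | ΔR² = 0 | ΔR² = 0.05 | ΔR² = 0.10 |
|---|---|---|---|---|
| 70 | 0.1 | 74.5 | 76.9 | 79.3 |
| 70 | 0.3 | 84.4 | 86.9 | 89.4 |
| 80 | 0.1 | 84.0 | 86.0 | 87.9 |
| 80 | 0.3 | 91.8 | 93.5 | 95.1 |

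The gain is about 2 points for an extra 5% of variance and 3-5 points for an extra 10%.

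**5. Which effects this concerns.** The standard error in SD units is √(2/720) = 0.0527. Powers of 70% and 80% therefore correspond to differences of 2.484 × 0.0527 = 0.131 SD and 2.802 × 0.0527 = 0.148 SD. At 0.20 SD the raw peak already has Φ(3.795 − 1.96) = 96.7% power, and adjustment at ρ = 0.5 gives Φ(3.795/0.866 − 1.96) = 99.2%.

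**The case against.** The strongest reply is that little is lost. Randomisation keeps the unadjusted comparisons valid. Item f is one of eight secondary items in Work Package 1, none with its own power target. With 720 per arm, adjustment matters only for differences of about 0.15 SD or less. Every secondary analysis is also corrected for type and severity of illness, which may already absorb part of what admission CRP would explain. The daily profiles get a longitudinal model that could include the admission value. All of this stands, and it limits the size of the point. It does not remove it: the longitudinal model's use of baseline is left open, the uncorrected analyses absorb nothing, and the floor at zero in the change score remains.

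The formulas also fit imperfectly. They assume near-normal data, equal SDs and linear tests, whereas the change score is bounded at zero, the Mann-Whitney test is allowed, and the fix redefines the outcome on the log scale. The power figures are therefore indicative, and with unequal SDs the ceiling at ρ = 0.5 need not hold.

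A reader might infer that the plan gives up a fixed 10-12 points of power. The documents do not support that: they give neither the correlation nor the starting power on which the figure depends. A reader might also infer that the comparison is biased, or that the admission value is used in no CRP analysis. No bias is shown, the change score does use it, and the profile analysis may.

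**Conclusion.** The point holds as a conditional efficiency and definition point on a secondary endpoint. Admission CRP is not a prespecified covariate for the peak or change comparison, and the peak may be the admission value, which makes the change non-negative and exactly zero for a child whose CRP only falls.

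The size cannot be fixed from the documents. With equal SDs and an assumed raw-peak power of 70-80%, the gain over the better planned comparison is at most about 12 points (from 70%) or 10 points (from 80%), at ρ = 0.5. It falls to about 2 points or less at ρ = 0.2 and 1 point or less at ρ = 0.8. On top of the planned correction for severity of illness, 2-5 points is a reasonable guide if admission CRP explains a further 5-10% of the variance. This is a worthwhile refinement of low severity, not a flaw in the trial's main conclusions.

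**What to change.** In 18.1.2 f and 20.3 f:

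- Define the peak as the highest CRP in samples taken after the admission sample.
- Make the main comparison a linear model of log peak CRP on treatment, with log admission CRP added to the covariates already listed.
- State that the longitudinal model for the daily profiles includes admission CRP as baseline.
- Keep raw peak and change from baseline as descriptive summaries by arm.

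This costs wording only, with no new samples or procedures, provided that admission CRP is recorded as the planned change score implies. The small downside is that a child without a post-admission sample contributes no peak. Report the number of such children in each arm.
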